#### Primary outcome

As the primary outcome, well-being will be assessed using the WHO Index-5 (WHO-5).^42^ WHO-5 is a five-item self-report questionnaire of current well-being. It is a unidimensional measure with responses rated on a 6-point Likert scale, ranging from *at no time* (0) to *all the time* (5). Lower scores indicate the worst possible quality of life, and higher scores indicate the best possible quality of life.

#### Secondary outcomes

As secondary outcomes, infertility-related stress, depression and anxiety will be assessed. The Fertility Problem Inventory—Short Form (FPI-SF)^43^,^45^ is a 27-item self-report instrument designed to assess perceived infertility stress based on a comprehensive approach. FPI-SF includes four domains: social concern, need for parenthood, rejection of a child-free lifestyle and couple’s relationship concern. The social concern domain involves being sensitive to comments, reminders of infertility, experiencing feelings of social isolation and feeling disconnected from family or peers (eg, ‘When I see families with children, I feel left out’). The need for parenthood domain is connected to viewing parenthood as a fundamental or essential life goal and strongly identifying with the role of being a parent (eg, ‘As long as I can remember, I’ve wanted to be a parent’). Rejection of a child-free lifestyle domain refers to the belief that future satisfaction or happiness is contingent on having a child, accompanied by a negative perspective on a lifestyle without children (eg, ‘Not having a child/another child would allow me time to do other satisfying things’). The couple’s relationship concerns domain involves challenges in discussing infertility, worries about how infertility might affect the relationship and concerns about its impact on the couple’s sexual life (eg, ‘My partner doesn’t understand the way the fertility problem affects me’). The FPI-SF is rated on a 6-point Likert scale, ranging from *strongly disagree* (1) to *strongly agree* (6).

The Patient Health Questionnaire for Depression and Anxiety (PHQ-4)^46 47^ is a 4-item self-report instrument widely used to identify individuals who may be suffering from anxiety, depression or both. It includes two subscales: the depression subscale and the anxiety subscale. The depression subscale comprises the two core criteria for depressive disorders (eg, ‘Feeling down, depressed or hopeless’). The anxiety subscale encompasses the two core criteria for generalised anxiety disorder (eg, ‘Feeling nervous, anxious or on edge’), which have also been proven to be effective screening items for panic disorder, social anxiety and post-traumatic stress disorder. The PHQ-4 is rated on a 4-point Likert scale, ranging from *not at all* (0) to *nearly every day* (3). Higher scores are strongly associated with functional impairment and disability.

#### Mechanisms of change

Mindfulness, self-compassion, psychological flexibility and infertility-related self-efficacy will be assessed as mechanisms of change.

The Five Facet Mindfulness Questionnaire—Short Form (FFMQ-SF)^48^,^50^ is a 24‐item self‐report questionnaire highly sensitive to change, aiming to assess different mindfulness skills. The FFMQ-SF is rated on a 5-point Likert scale and comprises five subscales: observing (eg, ‘I pay attention to how my emotions affect my thoughts and behaviour’), describing (eg, ‘I can easily put my beliefs, opinions and expectations into words’), acting with awareness (eg, ‘When I do things, my mind wanders off, and I’m easily distracted’), non-judging of inner experience (eg, ‘I tell myself I shouldn’t be feeling the way I’m feeling’) and non-reactivity to inner experience (eg, ‘I perceive my feelings and emotions without having to react to them’). Higher scores are indicative of higher levels of mindfulness facets.

The Self-Compassion Scale—Short Form^51^,^53^ is a 12-item self-report measure used to assess the ability to deal with and embrace one’s feelings of suffering based on a sense of warmth, connection and concern. This instrument is widely used in clinical practice for its high sensitivity to change. It integrates two subscales: Self-Disparagement (eg, ‘When I fail at something important to me, I become consumed by feelings of inadequacy.’) and Self-Care (eg, ‘I try to be understanding and patient towards those aspects of my personality I don’t like.’). The total score is an overall suggestion of self-compassion, with higher scores linked to more self-compassion.

The Psy-Flex^54 55^ is a context-sensitive self-report measure aiming to assess psychological flexibility, defined as the competencies that guide the individual to change and facilitate behaviours that are more adaptive and valued by the individual, following the ACT theoretical model. This instrument includes six items, rated on a 5-point Likert scale, each referring to one of the central skills when developing psychological flexibility. Higher scores are indicative of higher levels of psychological flexibility.

The Infertility Self-Efficacy Scale (ISE)^56 57^ is a self-report instrument to assess infertile patients' perception of their ability to use their own cognitive, emotional and behavioural competencies for dealing with infertility diagnosis and medical treatments. ISE comprises 16 items rated on a 9-point Likert scale. A higher total score indicates higher confidence levels in perceived capabilities to deal with infertility and its demands.

### Data analysis plan

Statistical analysis will be conducted using IBM SPSS Statistics V.27. Descriptive statistics will be performed. Specifically, for the continuous variables, means and SD or SE of the mean will be obtained, and for categorical variables, absolute numbers and percentages (%) will be calculated. Differences between groups will be assessed through t*-*tests and χ^2^ tests. mITT (all participants who will complete T1 and T2) and PP (only participants who will receive a sufficient dose) analyses on primary (well-being) and secondary outcomes (infertility-related stress, depression and anxiety) measured at T1, T2 and T3 will be performed to explore limited efficacy on the study outcomes.

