### Sample size

G*Power calculations for within-between interaction Analysis of Variance (ANOVA) repeated measures (two-conditions, two-time points), assuming a p=0.05, effect size *f*=0.25, power=0.95, recommend a sample size of 54. Assuming participation and retention rates of 60% and 34% (observed in similar apps), we will recruit n=180 participants. This sample size is in accordance with Sim and Lewis^37^ recommendation of at least 50 participants for feasibility studies.

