#### Feasibility outcomes

Aligned with Bowen *et al*,^35^ the current study uses several feasibility dimensions to evaluate the KindMap intervention and study protocol. For the KindMap intervention, demand, adaptation, acceptability, implementation, practicality, integration and limited efficacy dimensions will be assessed.

Demand will be assessed by programme adherence (eg, number of users and percentage of modules completed). Adaptation will be assessed by the differences in the hours spent and total number of visits of participants engaging with the KindMap in Portuguese and English. Acceptability will be assessed by user-reported programme satisfaction, perceived usefulness of each module and meditation practices and willingness to recommend the KindMap to peers. Implementation will be assessed by responses to open-ended questions regarding technical problems, the suitability of the 8-week recommended engagement period and barriers and facilitators of use. Practicality will be assessed by the number of participants who use the KindMap as intended (complete eight modules), complete six out of eight modules during the 8–10-week recommended engagement period, and the time taken to use the web app as intended. Integration will be assessed by participants’ perception of using the KindMap skills in everyday life and their willingness to continue doing so. Limited efficacy will be assessed by the effect size estimations of primary and secondary self-reported outcomes changes in the EG-KindMap versus WL-CG. More specifically, Modified Intention-to-Treat (mITT, all participants randomised) and Per-Protocol (PP, only participants who received a sufficient dose) analyses on primary (well-being) and secondary outcomes (infertility-related stress, depression and anxiety) measured at T1, T2 and T3 will be performed.

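### No between-group analysis stated in the protocol adjusts the T2 score for T1, so the limited-efficacy intervals will be wider than they need to be

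*Protocol article*

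**What the plan says.** Three places in the protocol article bear on how the arms will be compared.

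- **Sample size.** The calculation is for a "within-between interaction Analysis of Variance (ANOVA) repeated measures" with two conditions and two time points, at f = 0.25 and alpha 0.05: "power=0.95, recommend a sample size of 54".
- **Feasibility outcomes.** "Limited efficacy will be assessed by the effect size estimations of primary and secondary self-reported outcomes changes in the EG-KindMap versus WL-CG". The target is therefore a between-arm comparison of change.
- **Data analysis plan.** After the descriptive statistics comes "Differences between groups will be assessed through" t-tests and chi-square tests. The variable, the time point and the type of score (raw or change) are not given. The next sentence announces modified intention-to-treat and per-protocol analyses of the outcomes at T1, T2 and T3, and names no model.

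No section mentions a baseline-adjusted comparison. The Randomisation section places allocation after completion of T1, so every randomised participant has a T1 score.

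**The concern.** The t-test sentence can be read in three ways, and each leaves something to improve.

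1. A t-test on T2 scores makes no use of T1.
2. A t-test on change uses T1, but gives it a fixed coefficient of 1 instead of the coefficient the data support.
3. A baseline comparison tests differences that randomisation has already made a matter of chance. The outcomes are then left with the change effect sizes of the Feasibility outcomes section, which are also unadjusted.

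The estimated effect and its interval are the efficacy product of this study, and they are meant to inform a later, suitably powered trial. With 2:1 allocation and heavy expected attrition, the control arm may hold only 12 to 20 completers. Intervals will be wide and chance baseline imbalance will be common. At 24 and 12, the standard error of a baseline difference is √(1/24 + 1/12) = 0.35 SD. A T2-only comparison carries rho times any such imbalance into the estimate, and ANCOVA removes it.

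**Working it through.** **Inputs.** From the Sample size section: f = 0.25, alpha 0.05, power 0.95, N = 54, and "Assuming participation and retention rates of 60% and 34% (observed in similar apps), we will recruit n=180 participants". From the Randomisation section: 2:1 allocation. The T1–T2 correlation rho is not given. I take 0.5 and show 0.3 to 0.8. Outcome SDs are taken as equal at T1 and T2, and results are in SD units.

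**Step 1: reproduce 54.** For the 2×2 interaction, lambda = f²·N·2/(1 − rho), with 1 and N − 2 degrees of freedom. At rho = 0.5 and N = 54, lambda = 0.0625 × 54 × 2/0.5 = 13.5 and power is 0.9501. At N = 53 power is 0.946. So 54 is the smallest N that reaches 0.95, and rho = 0.5 reproduces the stated figure exactly (for equal arms). In this formulation f = 0.25 is a difference in change of 4f = 1.0 SD.

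**Step 2: relation between the sized test and a t-test.** With two time points, the interaction F-test and a two-sample t-test on T2 − T1 are the same test. Both give 95.0% power at 27 and 27.

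**Step 3: variance of the estimated difference,** as a multiple of σ²(1/n₁ + 1/n₂):

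- T2 only: 1
- Change: 2(1 − rho)
- ANCOVA on T1: 1 − rho²

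The ratio of ANCOVA to T2-only is 1 − rho². The ratio of ANCOVA to change is (1 − rho²)/[2(1 − rho)] = (1 + rho)/2.

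| rho | ANCOVA / T2-only | ANCOVA / change |
|---|---|---|
| 0.3 | 0.91 | 0.65 |
| 0.5 | 0.75 | 0.75 |
| 0.7 | 0.51 | 0.85 |
| 0.8 | 0.36 | 0.90 |

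**Step 4: number of completers.** If both rates apply to the 180, 180 × 0.60 × 0.34 = 36.7, or about 24 and 12 at 2:1. If only retention applies, 180 × 0.34 = 61.2, or about 41 and 20.

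**Step 5: 95% interval half-width at rho = 0.5,** as t × √[variance multiple × (1/n₁ + 1/n₂)]. T2-only and change coincide at this rho.

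- 24 and 12, unadjusted: 2.032 × √0.125 = 0.72 SD
- 24 and 12, ANCOVA: 2.035 × √(0.75 × 0.125) = 0.62 SD
- 41 and 20, unadjusted: 2.001 × √0.0744 = 0.55 SD
- 41 and 20, ANCOVA: 2.002 × √(0.75 × 0.0744) = 0.47 SD

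The ANCOVA figures leave out the small cost of estimating the slope, about 1/(N − 4) in variance: 3% at N = 36 and 2% at N = 61. Including it gives 0.63 and 0.48 SD.

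**Step 6: the same gain as power,** for the 1.0 SD effect of the sizing at rho = 0.5. At 24 and 12, power is 0.785 for either t-test and 0.887 for ANCOVA. At 36 and 18, it is 0.925 and 0.975. For 95% power at 2:1, either t-test needs 63 completers and ANCOVA needs 48.

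**The case against.** The strongest reply is that the protocol never says the t-tests are the outcome analysis. They follow a sentence on continuous and categorical descriptives, which is the pairing that t-tests and chi-square tests fit, and the outcomes are scale scores for which chi-square has no evident role. The sentence may simply describe baseline comparisons. The outcome model would then be unnamed, and a condensed article may leave that to a fuller document.

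Much of this stands. A reader might infer that the protocol commits to unadjusted t-tests that contradict the sizing model and discard T1. The text does not support that:

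- The t-tests are not tied to any outcome or time point.
- A t-test on change is identical to the sized interaction and does use T1. The Feasibility outcomes section speaks of changes, which points that way.
- Even a T2-only test has the same power as the sized model at rho = 0.5. It is weaker only above 0.5 and stronger below: at 36 and 18, 92.5% against 99.2% at rho = 0.7, and 92.5% against 81.9% at rho = 0.3.

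It is also fair that change scores are valid under randomisation, that the gain over them shrinks to 10% of variance at rho = 0.8, and that the protocol itself says the sample is too small to determine efficacy.

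The reply does not remove the point. It concerns more than an unnamed model: the between-arm quantity the article does state, effect sizes of change, is itself less efficient than the T1-adjusted T2 difference, whichever reading of the t-test sentence is right.

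**Conclusion.** The point holds as an avoidable loss of precision combined with an ambiguous sentence. It is not a contradiction between the sizing and the analysis. Under every reading, no stated between-arm comparison adjusts T2 for T1. At rho = 0.5, adjustment removes a quarter of the variance and shortens the intervals by about 13% (0.72 to 0.62 SD, or 0.55 to 0.47 SD). Over rho 0.3 to 0.8 the variance saved runs from 9% to 64% against T2-only, and from 35% down to 10% against change. The size rests on a correlation the protocol does not give, on equal SDs at T1 and T2, and on 37 to 61 completers. The direction depends on none of these beyond a positive correlation large enough to repay one degree of freedom. Because efficacy is exploratory and is one of several feasibility dimensions, this is a change that should be made, not one on which the study stands or falls.

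**What to change.** In the Data analysis plan, state that for each primary and secondary outcome the T2 difference, KindMap-EG minus WL-CG, is estimated by ANCOVA with the T1 score of that outcome as covariate. A mixed model with a common baseline mean is an equivalent choice. Report the adjusted mean difference, the standardised effect and the 95% confidence interval as the limited-efficacy estimate, and align the effect-size sentence under Feasibility outcomes with it. State what the t-tests and chi-square tests are for. Describe baseline characteristics by arm without significance tests. Adjusting for language version is optional, since the Randomisation section describes language stratification only within KindMap-EG.

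The cost is a few sentences and one degree of freedom. No new data are needed, since T1 is complete for everyone randomised, and ANCOVA and mixed models are standard in the software named.

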### Randomisation

Figure 1 shows the expected flow of participants throughout the study. Consenting participants will be randomised in a 2:1 ratio through computer-generated randomisation after completing the T1 assessment. Randomisation will be guaranteed by a third researcher (different from the two responsible for enrolment and allocation of the participants to the EG-KindMap and WL-CG groups) who will only know the participants’ code. Participants randomised into KindMap-EG will be stratified into a Portuguese or English-speaking group. All participants will be informed of the randomisation results.

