**Figure 3 F3:**
[figure not shown]
KindMap screenshots of the mobile app.

After completing each module, users unlock the following module and have automatic access to the ‘Practices’ section activities/meditations to practice between modules. The final topic addressed is a wrap-up of the programme designed to encourage users to recognise the changes they have undergone since the first module, acknowledge the therapeutic skills they have acquired/developed and motivate them to incorporate these skills in their everyday lives and upcoming difficult situations.

Every time users access the web app, they are invited to answer two brief questions about their well-being state and state of mindfulness (present moment awareness), using a 10-point Likert scale ranging from *not at all* (1) to *very/strongly* (10).

There will be no special criteria for discontinuing or modifying allocated interventions.

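### The modified intention-to-treat set is defined in two incompatible ways, and the version in the data analysis plan is a T2-completer set

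*Protocol article*

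**What the plan says.** The Feasibility outcomes section, describing how limited efficacy will be assessed, names the set as "Modified Intention-to-Treat (mITT, all participants randomised". The Data analysis plan names it as "mITT (all participants who will complete T1 and T2". Both sections pair it with a per-protocol set of participants who received enough of the intervention. Both apply it to well-being (the primary outcome), infertility-related stress, depression and anxiety at T1, T2 and T3.

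On timing, the Randomisation section states: "Consenting participants will be randomised in a 2:1 ratio through computer-generated randomisation after completing the T1 assessment". The Procedures section gives the same order. Under Study design, T3 is collected in the KindMap arm only, so T1 and T2 carry the between-arm comparison.

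The Sample size section plans on 60% participation and 34% retention, taken from similar apps, with 180 to be recruited. It does not say to which assessment the retention rate refers, or whether its denominator is people approached, enrolled or randomised.

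**The concern.** One label covers two different sets of people for the named primary outcome, and nothing in the article says which governs. The set in the Data analysis plan also depends on attendance at T2, a post-randomisation event. A comparison restricted in that way no longer has the full protection of randomisation, yet it would be reported under an intention-to-treat name.

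The conditions around T2 differ between arms. The trial is unblinded and participants are told their allocation. The KindMap arm uses an app without human support and has an additional feasibility questionnaire at T2. The waiting-list arm receives access to the app at that time. Completion could therefore differ by arm in its rate or its reasons, although the article gives no evidence that it will.

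Two things are at stake. The between-arm effect size is the measure of limited efficacy, and the article applies traffic-light criteria to each feasibility outcome, so the choice of set can enter the progression decision. In addition, two definitions leave room to choose between them once the data are known.

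**Working it through.** **1. The plan's own figure.** Inputs from the Sample size section: "repeated measures (two-conditions, two-time points"; "assuming a p=0.05"; and effect size, power and result, "0.25, power=0.95, recommend a sample size of 54". The correlation between time points is not stated; 0.5 is assumed here.

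- Noncentrality: λ = f² × N × m / (1 − ρ) = 0.0625 × 54 × 2 / 0.5 = 13.5, with 1 and N − 2 = 52 degrees of freedom.
- Power = 0.9501, and 54 is the smallest total that reaches 0.95. The figure reproduces.
- Other correlations give N = 106 (ρ= 0), 76 (ρ = 0.3) and 34 (ρ = 0.7).

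The calculation concerns a time-by-group interaction, that is, a between-arm difference in change. This matters for any statement about bias.

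**2. The two definitions side by side.**

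- Feasibility outcomes: everyone randomised.
- Data analysis plan: everyone with T1 and T2.
- Randomisation and Procedures: T1 is completed before allocation, so every randomised participant has T1.

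The T1 condition therefore removes nobody who was randomised. The second set equals randomised participants with T2, and it matches the first only if no T2 assessment is missed.

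**3. Size of the gap.** Let R be T2 retention among those randomised. The excluded share is 1 − R. Assuming that the 34% is this quantity, 1 − 0.34 = 0.66.

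| Reading of the 180 | Randomised | Analysed as completers | Excluded | Completers by arm at 2:1 |
|---|---|---|---|---|
| All 180 randomised | 180 | 180 × 0.34 = 61.2 | 118.8 | about 41 and 20 |
| 60% participation applied first | 180 × 0.60 = 108 | 108 × 0.34 = 36.7 | 71.3 | about 24 and 12 |

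The arm counts assume equal retention in the two arms. The excluded share is 66% on either reading. If the 34% describes retention to T3 instead, the loss at T2 is smaller and so is the gap.

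**4. Bias.** For a difference in change, selection matters only if T2 attendance is related to the change itself, and differently in the two arms. The article gives no figure for either, so no bias can be computed from it.

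**The case against.** **A reader might infer a specific bias.** Suppose that the retained 34% in the KindMap arm are the top of a trait correlated r with the raw T2 score, that the waiting-list arm is not selected at all, and that there is no true effect. The completer difference at T2 is then r × φ(0.412)/0.34 = r × 1.078, or 0.11, 0.22 and 0.32 SD at r = 0.1, 0.2 and 0.3. The arithmetic is right, but it is a worst case for a different contrast. The plan compares change. If the trait is equally correlated with T1 and T2 on the same scale, the shift in change is (r − r) × 1.078 = 0. Equal selection in both arms also gives zero. The article supplies no r, so these figures do not measure the bias in the planned analysis.

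**A reader might infer that two thirds will be lost.** That is an expectation from a planning rate without a stated time point or denominator. It is not an established loss.

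**A reader might call this the deciding result of the trial.** Limited efficacy is one of seven intervention feasibility dimensions, the analyses are described as exploratory, and the strengths and limitations box concedes that the sample cannot establish efficacy. On the other side, well-being is named the primary outcome and the traffic-light criteria cover every feasibility outcome, so the result may contribute to progression.

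**The plan attends to attrition.** It has three reminder emails, an exit questionnaire, and retention and withdrawal reasons as feasibility outcomes. These make attrition a measured result, but they do not settle who is analysed.

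**The set is called modified, its restriction is stated openly, and missing-data methods may sit in a document not shown.** All fair. The absence of an imputation method is not the criticism here. The criticism is that the published text defines the same set in two ways, and this stands whatever another document says.

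**Conclusion.** The contradiction is explicit and needs no calculation. One section includes everyone randomised; the other includes only T2 completers and keeps the intention-to-treat label. If the 34% is T2 retention among those randomised, the sets differ by about 66% of participants: about 61 against 180, or about 37 against 108. If it refers to T3, they differ by less. The direction and size of any bias in the between-arm change are unknown from the article.

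This should be corrected. It is not a fatal flaw, because the efficacy analysis is exploratory and one of several feasibility dimensions.

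**What to change.** - Use one definition in both sections: all randomised participants, analysed as allocated.
- Keep participants with T1 only, through multiple imputation or a likelihood-based model, using T1 scores and language in both arms.
- Treat app-use data with care. Module counts, and the ratings collected when users open the app ("they are invited to answer two brief questions about their well-being state and state of mindfulness"), do not exist for the waiting-list arm before T2. They can enter only an arm-specific imputation model for the KindMap arm, and users who stop opening the app will supply few ratings.
- Rename the T1-plus-T2 set completers and report it as a sensitivity analysis. A delta-shift check is optional.
- State the time point and denominator of the 34% retention rate.

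The cost is wording and a modest amount of extra analysis, with no new data. The gain over a completer analysis will be limited if T1 data predict T2 scores or dropout only weakly, and dropout that depends on unobserved outcomes would remain possible.
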